## Background

Inflammatory bowel disease (IBD) causes unpredictable bouts of gut inflammation, with acute illness, diarrhoea, and pain. In remission, many people with IBD live with fatigue, chronic abdominal pain and bowel urgency/incontinence [1]. There is no current cure for IBD, which usually starts in childhood or as a young adult. Most previous IBD research has focused on controlling inflammation. However, many people report continuing IBD-related fatigue (41%), abdominal pain (62%) and difficulty with continence (up to 75%) even when IBD is in remission [1–3]. Although patients in clinical remission may still have a burden of inflammation detected endoscopically or histologically, even patients with clinical and endoscopic/ histologic healing often continue to experience these symptoms. These symptoms limit peoples’ quality of life and ability to work and socialise. Patients feel that these symptoms are not taken seriously by health professionals and report that little help is given [2, 4, 5]. The James Lind Alliance IBD research priority-setting consensus put fatigue, pain and incontinence amongst the top 10 issues that IBD patients and clinicians want to be addressed by research [6].

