## Rationale for the choice of a cognitive behavioural intervention

Symptoms of fatigue, pain and urgency/incontinence have a major impact on quality of life of people with IBD [1–3]. Despite this, there has been remarkably little research on managing these troublesome IBD symptoms. Cognitive behavioural (CB) theories of these symptoms in other conditions suggest that disease factors trigger symptoms, but an interaction of cognitive, behavioural, emotional, environmental and physiological factors may strengthen and/or perpetuate them [7–10]. For instance, believing that pain and fatigue signal damage to the body (cognitions), may lead to avoidance of activity (behaviour) and distress (emotion). Distress activates the autonomic nervous system (physiology) which may generate additional symptoms, lead to poor sleep and perpetuate fatigue and pain. CB-based interventions which aim to alter these responses have been shown to reduce symptom severity and improve quality of life in other long-term conditions [11–13]. Online delivery of these interventions for chronic pain and fatigue appear effective in other conditions, with evidence of enhanced effects through the addition of minimal health care professional support [14–18].

Most studies in other medical conditions have focused on either fatigue or pain. Having separate CB interventions for each major symptom in IBD would create a substantive treatment burden. CB therapy (CBT) has been shown to be an effective treatment for irritable bowel syndrome (IBS) [12, 19]. As IBS is a multi-symptom condition, including abdominal pain alongside bowel disturbance, creating a single intervention to help manage all three of these IBD symptoms seemed justified. To test this empirically and in line the MRC framework for developing and testing complex interventions [20], we conducted a series of modelling studies and systematic reviews to define the specific cognitive and behavioural variables and treatment approaches that would benefit pain [21, 22], fatigue [2, 23] and urgency [21, 22] in IBD.

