## Methods: objectives, design and setting

### Objectives

The study aims to answer the following research questions:
Primary research question:
In people who report symptoms (scoring at least 5/10 on one or more symptoms on a 0–10 scale (where 0 = no problem and 10 = worst possible problem) and express a desire for intervention, does a facilitator-supported, tailored (to patient needs), online self-management programme for fatigue, pain and faecal urgency/incontinence in IBD improve IBD-related quality of life and global rating of symptom relief 6 months after randomisation, compared with care as usual?Secondary research questions:
2.Is there any difference between the groups in severity of symptoms of fatigue, pain and urgency/incontinence at 6 and 12 months after randomisation?3.Is there any difference between the groups in IBD-related quality of life and global rating of symptom relief 12 months after randomisation?4.Does prior medical optimisation of symptoms (in stage 3 of this programme) moderate the treatment response (i.e. do those receiving medical optimisation show greater treatment gains than those who do not) as measured by the primary outcomes?5.Do people with IBD in remission at trial commencement have a better response to treatment (primary outcomes) than those with active disease? (remission defined as faecal calprotectin within normal range (200 or under) and /or IBD control score [40] of 13 or over.6.Do baseline depression, or the presence of irritable bowel syndrome (Rome IV criteria) moderate treatment response to intervention (primary outcome measures)?7.Do changes in illness perceptions and behaviours, IBD specific anxiety and self-efficacy, and depression from baseline to 6 months mediate intervention effects on the primary outcomes at 12 months?8.Is a facilitator-supported, tailored, online self-management programme for fatigue, pain and faecal urgency/incontinence in IBD cost-effective?9.What are patients’ expectations and experiences of the intervention and what factors may have influenced the intervention implementation (qualitative work in process evaluation)?

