### Eligibility criteria

#### Inclusion criteria

Diagnosis of IBD (self-reported as having been medically diagnosed with IBD including patients with an ileo-anal pouch or stoma)18 years old or overLiving in England, Scotland or WalesHave participated in stage 2 of the programme (IBD-BOOST survey) and have self-scored one or more symptoms of fatigue, pain or urgency/incontinence as having an impact on their quality of life of 5 or more on a 0–10 scale when completing stage 2 (IBD-BOOST survey) or stage 3 (medical symptom optimisation) (whichever is the more recent)No ‘red flags’—see belowAccess to the online intervention via a computer or mobile device

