### Screening for ‘red flags’ and other risks

After participants consent, they will self-complete an online or paper copy checklist to check eligibility criteria above. Following consent, we will screen patients for ‘red flags’. These are potentially serious issues identified by our clinical co-investigators that may be undetected underlying causes of symptoms. If a participant’s responses indicate a potential red flag, the participant will be advised to seek a consultation with their health care team and only recruited to the trial once the symptoms have been adequately investigated.

We will also send consenting participants who have not already taken part in IBD-BOOST Optimise (stage 3 of the programme, who will have already done this) a kit for testing the faecal calprotectin level (see below and Additional file 5), but non-response to this test will NOT delay randomisation.

Additionally, item 9 (suicidal ideation) of the PHQ-9 in the baseline questionnaire (see below) will be reviewed to assess for risk of harm/suicidal ideation. If the participant has scored 2 or 3 (indicating frequent thoughts around suicidal ideation) then a risk assessment will be carried out by a psychologist by telephone. Participants assessed as low or medium risk will be able to continue into the trial, reminded of resources to access for further support and provided with an optional template letter to notify their GP. Appropriate urgent action will be taken for patients assessed as high risk and these individuals will not proceed into the trial.

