### Evaluation of moderators and mediators of treatment effects

The purpose of this additional quantitative process analysis is twofold:
To explore moderators of intervention effect

This will allow us to assess if there are any key subgroup effects and if the intervention should in future target specific groups of patients. For instance, if depression and disease activity moderate treatment effects, it may be best to focus the intervention on patients in remission and provide alternate treatment to people with depression. If medical treatment optimisation moderates outcome, then again this confirms best practice would be to provide optimised medical treatment before the intervention. Alternately, if there are no significant moderators of effects, the intervention may be generalisable to the broader IBD population.

Subgroup analyses to be investigated are those who underwent Optimise (stage 3); IBD in remission (see definition above); baseline measure of anxiety and depression (PHQ-9 and VSI); and ROME IV criteria for IBD met at baseline or not. These will be investigated by adding interactions terms to the analysis models used for the primary outcomes (UK- IBDQ and global symptom relief).
2.To explore mediators of change

Mediation analysis using structural equation models allows us to explore if a treatment effect occurs through hypothesised treatment mechanisms. We have based our choice of mediator measures on our cognitive behavioural model underpinning the intervention and described in our logic model (available on request form the lead author). Putative mediators have been mapped onto the key intervention components, i.e. the factors the intervention attempts to target to bring about improvements in symptom and quality of life. These include the following: the Visceral Sensitivity Index (VSI [56] and PHQ-9 [53] for symptoms of anxiety and depression; Self-efficacy for managing chronic disease 6-item scale [54]; Brief Illness Perception questionnaire [55]; All-or-nothing and avoidance/resting subscales from the Cognitive and Behavioural Responses to Symptoms questionnaire (CBRQ); IBD-Control [40]; faecal calprotectin [70]; satisfaction with outcome.

We are looking at whether proximal change in the mediators at 6 months predicts improvement in the outcomes at 12 months.

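### Rome IV status stands for IBS in participants with active IBD too, so an IBS-by-arm interaction fitted without disease activity may partly reflect activity

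*Protocol article*

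**What the plan says.** Under Objectives, research question 6 asks whether baseline depression or "the presence of irritable bowel syndrome (Rome IV criteria) moderate treatment response to intervention", judged on the primary outcomes. The section on evaluation of moderators and mediators lists the matching subgroup as "ROME IV criteria for IBD met at baseline or not". Everywhere else the article ties Rome IV to IBS. The Moderators and mediators list describes it as a symptom-based co-diagnosis.

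Active disease is not excluded. The disease criterion for entry is "Diagnosis of IBD (self-reported as having been medically diagnosed with IBD including patients with an ileo-anal pouch or stoma", and neither list of criteria requires remission. Research question 5 relies on this mix: "Do people with IBD in remission at trial commencement have a better response to treatment (primary outcomes) than those with active disease". Remission there means a calprotectin of 200 or under and/or an IBD-Control score of 13 or over.

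On symptoms, the Background says that IBD "causes unpredictable bouts of gut inflammation, with acute illness, diarrhoea, and pain". The rationale section says: "As IBS is a multi-symptom condition, including abdominal pain alongside bowel disturbance".

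The moderators are to be examined by adding interaction terms to the models for the two primary outcomes. Methods of analysis gives the covariates of those models: baseline outcome, stratification factors (diagnosis type and stage 3 participation), baseline fatigue, pain and incontinence, age and gender. No measure of disease activity is among them.

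**The concern.** A classification built from abdominal pain and disturbed bowel habit can be met because of IBS, because of inflammation, or both. If people with active disease meet it more often, the Rome-positive subgroup contains more active disease than the Rome-negative subgroup. Research question 5 expects a better response in remission. If that is true and IBS plays no part, Rome-positive participants will still show a smaller average effect.

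The existing covariates do not prevent this. Baseline fatigue, pain and incontinence enter as main effects, and main effects do not remove confounding of an interaction. Randomisation balances the arms. It does not balance one moderator against another.

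The protocol means to use these analyses to decide whether to target the intervention at particular groups of patients. An activity effect read as an IBS effect would misdirect that decision and would not cleanly answer research question 6.

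**Working it through.** **The protocol's own figures.** The Sample size section gives a design effect of 1 + 0.04 × 8 = 1.32, so 270/1.32 = 204.5 effective participants in the intervention arm. With 270 and 204, an effect size of 0.3 and a two-sided 5% level (assumed, not stated), power is 0.899. The stated 90% reproduces and is not affected by this point. The effective numbers are used below.

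**Formula.** Let the treatment effect be smaller by D in active disease, with no effect modification by IBS. The mean effect in a subgroup is then the remission effect minus D × P(active | subgroup). A model with arm, Rome IV and their interaction therefore gives an apparent IBS interaction of size

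D × [P(active | Rome+) − P(active | Rome−)].

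The bracket is the share of the activity interaction that is carried over.

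**Inputs.** The documents give neither the prevalence of active disease, nor Rome IV positivity by activity, nor D. All three are assumptions.

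**Middle case.** Take 40% active, with Rome IV met by 60% of active and 30% of remission participants.
- P(Rome+) = 0.4 × 0.6 + 0.6 × 0.3 = 0.42
- P(active | Rome+) = 0.24/0.42 = 0.571
- P(active | Rome−) = 0.16/0.58 = 0.276
- Share = 0.571 − 0.276 = 0.296 (unrounded). With D = 0.3 SD, the apparent interaction is 0.089 SD.

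**Range of the share carried over.**

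| Rome IV met: active vs remission | 30% active | 40% active | 50% active |
|---|---|---|---|
| 40% vs 40% | 0 | 0 | 0 |
| 50% vs 30% | 0.182 | 0.204 | 0.208 |
| 60% vs 30% | 0.265 | 0.296 | 0.303 |
| 70% vs 25% | 0.399 | 0.441 | 0.451 |
| 80% vs 20% | 0.535 | 0.584 | 0.600 |

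With D = 0.3 SD these shares correspond to 0 to 0.18 SD. The 60% vs 30% and 70% vs 25% rows give 0.08 to 0.14 SD.

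**Simulation of the middle case.** In 4,000 trials of 540 participants (no facilitator clustering, activity measured without error, D = 0.3 SD, no IBS effect), the mean IBS interaction was −0.089 when fitted alone. It was −0.001 with activity and activity-by-arm in the same model. The Monte Carlo standard error was about 0.003 for each. The ratio of those errors, 0.00291/0.00282 = 1.03, means that the joint model widens the interval by about 3% in this case.

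**Against sampling error.** With 270 and 204 effective participants and 42% Rome-positive, the unadjusted standard error of the interaction is √[(1/270 + 1/204)/(0.42 × 0.58)] = 0.19 SD. A bias of 0.08 to 0.14 SD is below one standard error. It raises the chance of a significant IBS interaction from 5% to about 7–11%.

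**The case against.** **Targeting needs only the observed subgroup.** If the aim is to decide whom to offer the programme, the effect by Rome IV status is a legitimate quantity whatever causes the symptoms, and research question 6 itself equates IBS with those criteria. This stands as a reason to keep the simple interaction. It does not justify interpreting the result as the role of IBS, which is how the question is worded.

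**The model is not fixed.** Adding interaction terms does not exclude a joint model, remission and Rome IV are listed together, and covariates may still change before unblinding. The analysis plan, which is not shown, may already deal with this. It would be wrong to infer that the protocol commits to fitting IBS without activity. What the article does fix is a symptom-only definition, named IBS, in a mixed population.

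**The association may be weak.** Every entrant scores at least 5 out of 10 for the impact of one or more symptoms, and the Background reports abdominal pain in 62% of people even in remission. Rome IV positivity might then differ little by activity, and with no difference the carry-over is zero. Nor do the documents show that Rome IV cannot tell the two conditions apart. Its items are not reproduced, and the overlap is inferred from brief descriptions.

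**Adjustment is imperfect.** IBD-Control is patient-reported, and the and/or remission rule can be met on it alone, so adjusting for it does not isolate inflammation. Calprotectin is more objective but may be absent: "non-response to this test will NOT delay randomisation". This stands, and it shapes the fix.

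**Conclusion.** The concern holds in conditional form. An IBS-by-arm interaction fitted without disease activity partly reflects activity if two things are true: activity modifies the treatment effect, and Rome IV positivity is more common in active disease. The protocol hypothesises the first and makes the second plausible, but establishes neither. The size cannot be computed from the documents. Over the assumed prevalences, 0 to 0.6 of any activity interaction carries over, and about 0.3 in the middle case.

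A reader might infer that the trial will report a poorer response in people with IBS. The figures do not support that: the bias is below one standard error under most of the assumptions tried, and a false significant result remains unlikely. A reader might also take the printed criteria for IBD literally. Every participant has IBD and the rest of the article says IBS, so this is a clerical slip.

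The analysis is exploratory and the primary comparison is untouched. This is a minor, worthwhile improvement.

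**What to change.** - Keep the Rome IV-by-arm interaction as a descriptive result.
- Report it also with baseline disease activity and activity-by-arm in the same model. Use faecal calprotectin where available and the protocol's remission status otherwise.
- Add a supportive estimate within participants whose baseline calprotectin is 200 or under, the protocol's own limit.
- When interpreting the subgroup, call it IBS-type symptoms (Rome IV).
- Correct IBD to IBS in the sentence that lists the subgroups.

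The cost is one main effect and one interaction in a secondary model, from baseline data already planned. The interval for the IBS interaction widens, by about 3% in the simulated middle case and by more if Rome IV and activity are more closely related. Where calprotectin is missing, adjustment rests on a patient-reported score and is incomplete. The supportive estimate uses fewer participants and will be less precise.

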## Methods: monitoring

### Data monitoring

A study monitoring and auditing plan will be produced. The risk assessment for the trial will be under continual review to assess relevance and applicability and to identify any actions that may be required. The study may be subject to inspection and audit by the sponsor and other regulatory bodies to ensure protocol compliance and adherence to GCP and the UK Policy Framework for Health & Social Care Research 2017. Protocol deviations, non-compliances or breaches from the approved protocol must be reported to the Sponsor R&D Office and PCTU within 24 h of becoming aware of the event.

### Harms

#### Assessment and management of risk

This is a low-risk study (as assessed by PCTU), although there is potential for participants to become distressed when thinking about their symptoms. The intervention site will include a link / website address to CCUK who provide support via their helpline, and contact details are included in the Participant Information Leaflet. The outcome measures include questions on anxiety and depression and the PHQ-9. The central research team will monitor responses to suicidal thoughts and contact the patient and undertake a risk assessment if necessary. At the end of the questionnaire, there are helplines listed that can offer support.

## Risks/benefits

### Stopping the trial

There is no Data Monitoring Committee for this low-risk study. The trial may be prematurely discontinued by the Sponsor or Chief Investigator on the basis of new safety information or for other reasons given by the Programme Steering Committee or REC concerned. There will be no formal stopping rules based on the intervention outcomes. In the unlikely event that the study is prematurely discontinued, active participants will be informed and no further participant data will be collected.

#### Adverse events (AEs)

Adverse events will be assessed using the follow-up questionnaire at the 6- and 12-month follow-up and may also be recorded by facilitators through communication with participants in the intervention arm. We will also attempt to capture any unforeseen consequences in the qualitative interviews.

#### Expected events

Expected AEs include planned/elective hospitalisations, or unplanned but expected hospitalisation due to flare-up of IBD: these are expected during the course of the trial and will not be collected or reported as serious AEs (SAEs).

After a SAE, a decision will be made by the trial team, after advice from the relevant authorities and the participant’s IBD team, as to whether the participant should be withdrawn from either their randomised treatment or from the trial. However, we do not envisage a situation, except death, in which a participant would need to be withdrawn. Arrangements will be made by the trial team for further assessment and management as agreed with the relevant authorities, GP and participant.

The investigator will provide the trial team with a 1-month follow-up report on all SAEs. Further monthly reports should be provided in the absence of resolution. These reports will be communicated to the Programme Steering Committee, REC, and to the local R&D office. Blank adverse event forms will be distributed to sites that are recruiting.

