## Economic evaluation methods

An economic evaluation using recommended methods [62] will be undertaken from the National Health Service /Personal Social Services and patients’ perspectives to evaluate the cost-effectiveness of the intervention at 12 months. The cost of the intervention, including facilitator’s contacts with each patient, website hosting and maintenance and facilitators’ training (venue, trainers’ and facilitators’ time, travel and subsistence, administrative support and materials) and supervision, will be evaluated.

Data on the use of health, social care and other services will be collected from all study participants using a study-specific IBD Resource Use questionnaire, developed within this Programme Grant, asking about contacts with primary and secondary care, investigations, medications, hospitalisations, employment and out-of-pocket expenses.

Unit costs will be sourced from national sources (e.g. Personal Social Services Research Unit: Unit Costs of Health and Social Care; Department of Health: NHS reference costs; British National Formulary; NHS Improvement: National tariff payment system) and will be applied to categories of resources used to estimate individual participant total costs. Health-related quality of life data will be collected using the EuroQoL EQ-5D-5L questionnaire.

We will follow the intention-to-treat principle, and missing data will be handled using multiple imputation approach. We will calculate quality-adjusted life years (QALYs) and total costs for each participant in the trial during the 12 months follow-up. We will evaluate the incremental QALYs and costs with allocation to the BOOST intervention and the intervention’s cost-effectiveness at 12 months follow-up. The costs and EQ-5D-5L utilities will be compared between the two study arms at 6 and 12 months after randomisation, with adjustments made for baseline values of outcome measures (costs in previous 3 months and EQ-5D-5L at baseline), stratification factors, fatigue, pain and urgency/incontinence at baseline, age and gender. Facilitators will be added as a random effect in the intervention arm only.

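### Unplanned admissions for IBD flare are taken out of SAE collection, and no comparison by arm is named as a safety outcome, although the resource use questionnaire already records hospitalisations in both arms

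*Protocol article*

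**What the plan says.** Under Expected events the article lists the category: "Expected AEs include planned/elective hospitalisations, or unplanned but expected hospitalisation due to flare-up of IBD". It then states the consequence: "these are expected during the course of the trial and will not be collected or reported as serious AEs (SAEs". The same section sends follow-up reports on SAEs to the Programme Steering Committee, the ethics committee and the local R&D office. Admissions outside the SAE definition do not enter those reports.

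Two other routes touch these events:

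- **Adverse events (AEs).** "Adverse events will be assessed using the follow-up questionnaire at the 6- and 12-month follow-up". The same sentence adds that events "may also be recorded by facilitators through communication with participants in the intervention arm".
- **Economic evaluation methods.** "Data on the use of health, social care and other services will be collected from all study participants using a study-specific IBD Resource Use questionnaire", with the instrument "asking about contacts with primary and secondary care, investigations, medications, hospitalisations, employment and out-of-pocket expenses". The Health economic measure section schedules it at baseline, 6 and 12 months and describes it as covering resource use due to IBD.

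On oversight, Stopping the trial says: "There is no Data Monitoring Committee for this low-risk study". Hospitalisation is not among the measures listed under Primary outcome measures or Other measures.

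**The concern.** That an event is expected is a sound reason not to report each case individually. It is not a reason to leave the event out of the comparison between arms. A background event that is common in the disease says nothing case by case, and in a randomised trial its meaning lies in whether the two arms differ.

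The event class is relevant here. The trial admits people with active disease (Objectives, research question 5), and the intervention arm keeps access to the programme during a flare (Facilitator support). If the programme changed flare admissions in either direction, the article's SAE summary would not show it. The route that remains for adverse events in general is ascertained unequally, so a difference seen there could not be separated from additional recording in one arm. The one source that asks both arms the same question is assigned to costing.

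**Working it through.** This is mainly a reading of the text. The arithmetic only sizes what a comparison by arm could show.

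**1. Where a flare admission would be recorded**

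| Route | Both arms alike? | Flare admissions included? | Planned use |
|---|---|---|---|
| SAE reports (Expected events) | Not applicable | No, excluded by rule | Safety, to the Steering Committee and ethics committee |
| AE item in the 6- and 12-month questionnaire (Adverse events) | Yes | Probably; still classed as expected AEs | Safety, no comparison named |
| Facilitator recording (Adverse events) | No, intervention arm only | Possibly | Safety, no comparison named |
| IBD Resource Use questionnaire (Health economic measure; Economic evaluation methods) | Yes | Yes, hospitalisations are a named item | Economic |

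The only route that is even between arms and names hospitalisations is the one with no stated safety use.

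**2. The plan's own figures**

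Inputs from Sample size: 340 per arm, 20% loss, ICC 0.04, about 9 analysed patients per facilitator, effect size 0.3.

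- Analysed per arm: 340 × 0.8 = 272 (stated 270).
- Design effect: 1 + 0.04 × 8 = 1.32. Effective intervention n: 270 / 1.32 = 204.5 (stated 204).
- Power, two-sided 5% (assumed, since no alpha is stated): SE = √(1/270 + 1/204) = 0.0928; 0.3 / 0.0928 − 1.96 = 1.27; power 89.9% (stated 90%).

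These reproduce. The point does not depend on them, except that 270 per arm is the expected number with questionnaire data.

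**3. What a comparison by arm could show**

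The article gives no flare-admission rate. Assumed 12-month control rates are p = 3%, 5% and 10%, with 270 per arm and no allowance for facilitator clustering.

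- Expected participants with an admission, control arm: 270 × p = 8.1, 13.5 and 27.
- Half-width of the 95% CI for the risk difference when both arms have rate p: 1.96 × √(2p(1−p)/270).
  - 3%: 1.96 × √(0.0582/270) = 2.9 points
  - 5%: 1.96 × √(0.095/270) = 3.7 points
  - 10%: 1.96 × √(0.18/270) = 5.1 points
- Power of a two-sided 5% test: Φ[(d − 1.96·SE₀)/SE₁], where d is the difference, SE₀ uses the pooled rate and SE₁ the separate rates. For 5% against 10%: SE₀ = √(2 × 0.075 × 0.925/270) = 0.02267; SE₁ = √((0.0475 + 0.09)/270) = 0.02257; (0.05 − 0.04443)/0.02257 = 0.247; power 60%.

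| Assumed control rate | Power, 1.5-fold excess | Power, doubling |
|---|---|---|
| 3% | 15% | 39% |
| 5% | 22% | 60% |
| 10% | 42% | 90% |

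These figures support an estimate with an interval rather than a hypothesis test.

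**4. Coverage in time**

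The only recall window stated is 3 months, for baseline costs (Economic evaluation methods). If the follow-up questionnaires used the same window, 3 of every 6 months, or half the follow-up, would be uncovered. That is an assumption; the follow-up window is not given.

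**The case against.** The strongest reply is that nothing is lost. The exclusion applies to these admissions as SAEs only, and the same section still calls them adverse events. Both arms are asked about adverse events at 6 and 12 months, hospitalisations are collected from everyone, and participants who flare are still sent the questionnaires. This stands. A reader might infer that the trial could not report an excess of flare admissions, or that these admissions go uncollected. The documents support neither.

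A reader might also infer that flare admission is the most plausible serious harm of the programme, for instance through delayed help-seeking. The article does not say so. The harm it names is distress (Assessment and management of risk). It also describes red-flag screening before randomisation, facilitators who are mostly IBD nurses, and continued access to clinics and the helpline in both arms. The point rests on how the event is handled, not on a claim that BOOST causes it.

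A third reply is that safety tables by arm are commonly left to the statistical analysis plan, which is not shown here. That plan may add such a table. But the article does more than stay silent: it states a rule that removes the events from the SAE pathway, and it should say where they are compared instead.

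The absence of a DMC should not be overstated either, since the trial may be stopped on new safety information or for reasons given by the Programme Steering Committee or the ethics committee. What remains is that the SAE reports described as going to that committee would not contain these admissions.

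**Conclusion.** The point holds in a limited form. By stated rule, unplanned flare admissions are outside SAE collection and reporting, and the article names no comparison of them by arm as a safety outcome. An evenly ascertained source exists and is planned only for costing. An excess could therefore be reported, but the article does not commit to reporting it as a harm.

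The size cannot be fixed from the documents. At assumed control rates of 3% to 10%, about 8 to 27 control participants with data would have an admission, and the risk difference would be known to within roughly 3 to 5 percentage points. This rests on the plan's 20% loss, no clustering and full recall coverage. It is an inexpensive improvement to what the trial can say about safety; it affects neither the primary analysis nor the trial's validity.

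**What to change.** Keep the exemption from individual SAE reporting. Add to Expected events that IBD-related hospitalisations from the IBD Resource Use questionnaire will be reported by arm as a safety outcome at 6 and 12 months:

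- the number of participants with at least one admission, and the number of admissions;
- unplanned admissions separately, if the questionnaire distinguishes them;
- the risk difference with a 95% CI, for estimation rather than as a test;
- the counts, supplied to the Programme Steering Committee.

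Confirm that the hospitalisation item covers each full 6-month interval, and state the recall window.

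The cost is one further table from data already planned, provided the items are worded suitably; the questionnaire itself is not shown, so this needs checking. There are limits to report with it. Participants are unblinded and self-report, so errors may differ between arms. About 270 per arm are expected to have data. Power for a modest excess is low, so a wide interval should not be read as evidence of no difference.
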